#### Safety of probiotics

Besides the already mentioned desirable attributes of an anti BV probiotic - adherence to the epithelial cells of the vagina, apoptosis of pathogenic microbes, production of H2O2 and of bacteriocins antagonistic to the growth of atypical microorganisms, as well as anti-TH2 activity - a probiotic must be safe.

Lactobacilli and bifidobacteriae are, in principle, considered to be safe because they are components of the comensal human flora and due to the fact that they have been used for a long time in food industry and in douches, even by pregnant women, without harmful effects [31,56,58].

Although lactobacilli have been identified in blood cultures and cultures of other organs, infections by lactobacilli are rare (30). Positive hemocultures for lactobacilli occurred in 0.24% of patients in a Finish study and in 0.1% in French patients; the infections occurred in patients with immunodeficiency [31,32]. The induction of infection has already been directly or indirectly tested by several studies on probiotics and none of the strains caused morbidity [58].

### Evidence found by trials on the effectiveness and safety of tested lactobacilli against BV

The choice of a probiotic, like that of any medical technology, requires that its effectiveness and safety are verified and so, the evaluation of these attributes, conducted by clinical trials _ preferably those randomized, controlled and double-blind_ is an important requirement for its regular use in human beings.

### Summary of trials available on the subject

a. Reid et al, 2001 [35] - Prospective study with a group of 10 asymptomatic women, with history of recurrent urogenital infection, including 6 asymptomatic cases of intermediate degree infection/BV, treated with an oral solution containing selected lactobacilli (Lactobacillus rhamnosus GR-1 e Lactobacillus fermentum TC-14), twice a day, for 14 days. No adverse side effects were reported and adherence to treatment was considered excellent. The 6 asymptomatic cases of intermediate degree infection/BV were cured after the first week of treatment and remained normal during follow-up (between 1 and 3 months).

b. Reid et al, 2001b [37] - Randomized controlled trial, comparing 4 probiotics: 3 of them were formed of 2 selected lactobacilli strains (Lactobacillus rhamnosus GR-1 and Lactobacillus fermentum TC-14) in different dosages: 1 dosage (2 groups), 2 dosages (1 group); the 4th group was considered the placebo because the lactobacilli used had no outstanding properties. Sixty percent (60%) of women presented BV or intermediate degree infection; 1/3 of them presented BV at the beginning of the study. Forty-two (42) asymptomatic women were randomized; the technician that evaluated the Nugent was blinded, as well as the researchers and the patients, except those receiving 2 daily dosages. Probiotics were orally taken (capsules) for 28 days. No adverse side effects were reported and adherence to treatment was considered excellent. The results were favorable to probiotics as compared to placebo; the best results against BV were observed in the group of patients who received 2 dosages a day (close to 90% effectiveness for BV). These results remained unchanged for a month after the treatment had finished.

c. Reid et al, 2003 [34] - Randomized, double-blind placebo-controlled trial (patients and researchers) to test the safety and prevention/treatment of asymptomatic urogenital infections, including BV. A population of 64 asymptomatic women in their fertile years used, once a day, a capsule with 2 types of selected bacilli (Lactobacillus rhamnosus GR-1 and Lactobacillus fermentum TC-14), with a concentration of each bacillus per capsule superior to 1 million or of placebo, for 60 days. The adherence of patients was considered excellent. Patients, monitored throughout the study, did not report side effects. Close to 40% of the cases of asymptomatic BV improved (they became intermediate stage) at the end of treatment, in comparison with 13% of the placebo group (p = 0.02). There was also significant reduction in the presence of Monilia and of E.coli in the group treated, versus the placebo group. However, the efficacy decreased after a 30 day-follow up.

d. Shalev, 2002 [38] - Randomized controlled trial, with crossover, comparative of the ingestion of yogurt containing lactobacilli acidophilus and pasteurized yogurt, in a total of 46 women for prophylaxis of recurrent BV. Significant statistical increase was observed as to the number of lactobacilli acidophilus in the vaginal mucosa and also a significant statistical decrease of BV cases (p < 0.001) occurred during the period of treatment with lactobacilli, as compared to the period when groups ingested pasteurized yogurt.

The above studies _small but consistently in favor of lactobacilli probiotics _ indicate that the ecologic treatment of BV through the colonization of vagina by exogenous lactobacilli is an alternative worth trying, both for BV and preterm delivery. However, the effectiveness of probiotics regarding the consequences of BV, i.e., preterm delivery and neonatal morbidiy, although plausible, has not been reported yet. It is important to remark that, despite the fact that none of the mentioned trials enrolled pregnant women, Lactobacilli rhamnosus have been used in a controlled clinical trial in pregnant women [61], side effects not being observed.

On the other hand, the probability of a test yielding benefits for health depends on the frequency of the problem, the ability of the test to detect the condition and to what extent early treatment is better than late intervention [62]. The lead time (time lapse between the detection and the moment in which the condition to be avoided might have occurred without the screening) needed to change favorably the natural history of a problem, varies in different diseases, different cases and depends on the treatment [63].

In this project, it is assumed that the necessary lead time to prevent spontaneous preterm delivery, associated to infection, depends on the moment (gestational age) at which vaginal infection occurs, on the kind of infection and on the mother (fetus)'s response to it, as well as on the moment the test is conducted regarding the development of the ominous infectious/allergic process and on the ability of the treatment to subdue the infection at the occasion (timing) it is conducted.

Thus, the rationale for the trial is based on the hypotheses that: a) the observed lack of efficacy of antibiotics may, in part, be attributed to lead time - the intervention would have occurred too late _, in part to bacterial resistance, in part to toxicity of the antibiotics used and, finally, in part, to an inflammatory process similar to allergy [27-29], and b) probiotics have more favorable attributes (bacteriotherapy plus immunomodulation) and, supposedly, less adverse events, to deal with bacterial vaginosis and preterm delivery, provided that they are given within an adequate lead time and dosage for an effective intervention.

## 2. General Objectives

To estimate the effectiveness of the early administration of specially formulated probiotics to pregnant women with bacterial vaginosis or an intermediate degree infection to prevent the occurrence of spontaneous premature birth and related neonatal mortality and morbidity.

### 2.1. Specific objectives

a- To assess the presence of bacterial vaginosis and intermediate degree infection in asymptomatic pregnant women, with no risk/indication of elective preterm delivery, admitted to prenatal care after the 8th and before the 20th week of gestation.

b- To investigate whether the study intervention can lower the vaginal pH and the Nugent score.

c- To asses the effectiveness of an early intervention with special probiotics to treat bacterial vaginosis/intermediate infection and to prevent spontaneous preterm delivery and associated neonatal/infant conditions in positive women, according to item *a*, by conducting a controlled, randomized, double-blind trial.

d- To analyze the association between the concentration of selected cytokines at cervicovaginal mucosa and the Nugent score, and the < 34 weeks' gestation prematurity rate, in both study subgroups.

e- To analyze the association of selected genetic polymorphisms and the occurrence of a) bacterial vaginosis or intermediate degree infection and b) preterm birth, in both study subgroups.

## 3. Methods

Asymptomatic pregnant women, admitted after the 8th and before the 20th week of pregnancy in selected public prenatal care services, in the city of Rio de Janeiro, will be evaluated to identify a) excluding clinical conditions, mainly those related to the presence of pathological conditions associated with elective preterm delivery, to symptomatic vaginal conditions and to current, or within the past two weeks, use of antibiotic therapy and b) pregnant women with previous history of preterm delivery. Gestational age will be determined by the date of the last menstrual period and through ultrasound results, the last one being privileged. Women who test positive to syphilis, toxoplasmosis, gonorrhea and HIV will be excluded. Other absolute exclusion criteria are: multiple gestation, istmo-cervical incompetence (cerclage in current gestation), fetus with major congenital malformations in current gestation, insulin dependent diabetes mellitus, systemic arterial hypertension under medication, antibiotic therapy after the 8^th ^week of the current gestation, clinical suspicion of low urinary tract infection, chronic asthma requesting intermittent therapy, continuous or recent corticotherapy (up to one month), hemolytic perinatal disease; systemic eritematous lupus. Relative exclusion criteria, i.e, only if observed at the moment of the evaluation, are: bacterial vaginosis or tricomoniasis with laboratory confirmation, HPV (those with macroscopic lesions in the genitalia or microscopic pre-cancerous lesions).

After written informed consent, vaginal pH assessment will be performed; patients with a pH < 4.5 will be excluded. Then, cervicovaginal smear will be obtained to evaluate the presence of BV or intermediate degree infection, using the Nugent method. Women with a Nugent score under 4 will be excluded from the trial.

### Ancillary analyses

Vaginal fluid and oral mucosa samples will also be obtained to allow for the evaluation of selected cytokines (IL-1beta, IL-1ra, IL-6, IL-8 and IL-10) and related genetic polymorphisms, respectively, from women with a pH> 4.4 who have consented. Furthermore, vaginal smear, cervicovaginal fluid and oral samples will be collected from a subsample of the women with a pH < 4.5 for comparison purposes. Gram-stained vaginal smears will be further analysed to determine the number of leukocytes per epithelial cell and the proportion of parabasal epitheliocytes to allow for the detection of moderate or severe aerobic vaginitis.

### 3.1. Randomization process

It was stratified for the factor history of preterm delivery (HPD), and blocked by using a permuted block design. Stratified randomization was attained by producing one blocked and randomized list for each stratum. Blocks of size 8 were specified for the strata of non HPD; for the group of HPD, blocks of size 4 have been adopted. The sequence for randomization was electronically generated by an independent research assistant.

Women with a Nugent score between 4 and 10 will be randomized, after a second written informed consent, as soon as possible. Research nurses responsible for allocation are not directly involved with prenatal care, i.e., with clinical screening. Allocation will be concealed by sealing both placebo and intervention capsules, identical in aspect, in sequentially numbered identical containers according to the allocation sequence. Besides the pregnant women, doctors/nurses and researchers/evaluators (assessment of outcomes, including Nugent score and other lab procedures) are to be blinded to the randomization process.

The trial will test two lactobacilli strains, Lactobacillus rhamnosus GR-1 and Lactobacillus fermentum RC-14, the latter presently denominated Lactobacillus reuteri RC-14, developed and studied by Reid et col [33-36] as earlier mentioned. Each capsule contains an amount superior to one million bacilli of each strain. Each participant will receive, from the research nurse, one box with six bottles, box and bottles equally numbered, of probiotics/placebo, each bottle containing 30 capsules, corresponding to a maximum intervention period of 12 weeks. Participants will be then instructed to maintain the box at the refrigerator (not at the freezer) and to take two capsules per day, along a period that may vary from six to twelve weeks, depending on the participant's gestational age at the moment of enrollment in the study. Enrolled women will be free to contact the research assistant nurses or the research doctor; one week after randomization, they will be contacted by telephone for information about treatment. More detailed questioning will be made at each routine prenatal visit until the completion of the trial (around the 24-25th week of gestation) regarding adhesion/adherence, adverse events and clinical intercorrences, according to a previously designed form. Adherence will be fostered, when appropriate. At the post treatment prenatal care visit, randomized women will be asked to bring back all bottles; capsules remaining in the bottles they return will be counted. Adherence is defined as at least 6 wks of treatment.

At the post-treatment prenatal care visit, vaginal pH will be assessed; cervicovaginal smear and fluid will be collected to determine the post intervention Nugent score and levels of the selected cytokines in order to evaluate changes in those parameters (secondary results).

A detailed and extensive protocol was developed. Standard Operational Procedures were elaborated to cover the logistics and operational aspects of the trial. They cover not only details related to the whole screening process and materials' collection, transportation and storage but also elements that are relevant to the randomization process, including creation and protection of the allocation sequence, labeling of bottles and boxes, as well as the filling in and sending out the Case Record Forms.

A special software has been developed to acquire and store collected information. A workshop for training purpose and a pilot study were carried out in each of the services involved in the study; the protocol was revised accordingly.

Patients flow in accordance to the protocol is summarized in Figure 1.

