**Methods/Design:**

Women attending public prenatal care services in Rio de Janeiro will be screened to select asymptomatic pregnant women, less than 20 weeks' gestation, with no indication of elective preterm delivery. Those with vaginal pH > = 4.5 and a Nugent score between 4 and 10 (intermediate degree infection or bacterial vaginosis) will be randomized to either the placebo or the intervention group, after written informed consent. Intervention consists in the use of probiotics, Lactobacillus rhamnosus GR-1 and Lactobacillus reuteri RC-14, 2 capsules a day, each capsule containing more than one million bacilli of each strain, for 6-12 weeks, up to the 24th-25th wk of gestation. Ancillary analyses include quantification of selected cervicovaginal cytokines and genotyping of selected polymorphisms. The randomization process is stratified for history of preterm delivery and blocked. Allocation concealment was designed as well as blinding of women, caregivers and outcome evaluators. The study will be supervised by an independent monitoring committee. Outcomes under study are preterm delivery (< 34- < 32 weeks of gestation) and associated neonatal complications: early neonatal sepsis, bronchopulmonary dysplasia, periventricular leukomalacia, necrotizing enterocolitis, and prematurity-related retinopathy; definitions were adapted from those recommended by the 2002 version of the Vermont-Oxford Network. Trial registration at NIH register: NCT00303082.

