### 3.4. Data analysis

A post randomization table will comprehend the distribution of all relevant variables. Outcomes will be analyzed according to intention to treat and effective treatment. The Student t test, the X2 test for proportions and the Fisher test will be used in the preliminary data analyses. In those cases where the Student test does not apply due to non Gaussian distribution, the Mann-Whitney test will be used. Outcomes will also be analyzed according to subgroups of selected risk factors at admission and categories of severity of the infectious process, according to the study biological markers. The association between knowledge based selected factors and dichotomous or continuous outputs will be investigated under the framework of generalized additive models to handle non linear predictors as well as non Gaussian responses.

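### A flat six-week adherence rule is out of reach for the latest starters on most readings of the stop, and for any woman who delivers or loses the pregnancy within six weeks of starting

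*Protocol article*

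**What the plan says.** The protocol article gives one definition of adherence, in section 3.1: "Adherence is defined as at least 6 wks of treatment". The same section makes planned duration variable. The intake is two capsules daily, and the course is described thus: "along a period that may vary from six to twelve weeks, depending on the participant's gestational age at the moment of enrollment in the study". Each receives six bottles, "each bottle containing 30 capsules, corresponding to a maximum intervention period of 12 weeks".

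The abstract describes treatment "for 6-12 weeks, up to the 24th-25th wk of gestation". Section 3.1 places the end of the treatment phase only approximately; questioning about adherence runs "until the completion of the trial (around the 24-25th week of gestation".

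On entry, section 3 takes women "admitted after the 8th and before the 20th week of pregnancy", and the abstract says "less than 20 weeks' gestation". Section 3.1 adds that randomisation follows the Nugent result and a second consent.

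Section 3.4 (Data analysis) states: "Outcomes will be analyzed according to intention to treat and effective treatment". It does not say how the effective-treatment set is formed.

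**The concern.** A fixed minimum number of weeks is applied to women whose planned treatment differs in length. This has two consequences, which should be kept apart.

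- **Late entry.** The latest entrants may have less than six weeks between start and planned stop, so perfect compliance can still be labelled non-adherence. A woman with a long planned course is adherent after taking only part of it.
- **Early delivery or loss.** To count as adherent a woman must stay pregnant and on treatment for 42 days. One who delivers or loses the pregnancy sooner is non-adherent whatever she took. Membership of the set then depends on the event that the trial is meant to compare.

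Only the second can distort the comparison between arms. It matters because the deliveries it removes are the most extreme cases of the < 32 and < 34 week outcomes.

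**Working it through.** **The plan's own figures.** Supply: 6 bottles × 30 capsules ÷ 2 per day = 90 days (12.9 weeks), which covers the stated 12-week maximum of 84 days. Sample size: for 6% against 3%, two-sided 0.05, 80% power and pooled variance, n per arm = [1.960·√(2 × 0.045 × 0.955) + 0.842·√(0.06 × 0.94 + 0.03 × 0.97)]² ÷ 0.03² = 749. That gives 1498 in all, which agrees with the stated 1500. The sample size is not in question; 750 per arm is used only for the event counts below.

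**Late entry.** In completed weeks, the latest entry is 19w6d (day 139) and the threshold is 42 days. Time available = stop − start. The share assumes starts spread evenly over the 84 days from 8w0d to 19w6d; the article gives no entry distribution.

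| Stop read as | Days left from 19w6d | Latest start allowing 42 days | Start days shut out | Share |
|---|---|---|---|---|
| 24w0d (day 168) | 168 − 139 = 29 | 168 − 42 = 126, i.e. 18w0d | 13 of 84 | 15% |
| 25w0d (day 175) | 175 − 139 = 36 | 175 − 42 = 133, i.e. 19w0d | 6 of 84 | 7% |
| 25w6d (day 181) | 181 − 139 = 42 | 181 − 42 = 139, i.e. 19w6d | 0 of 84 | 0% |

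If starts are instead spread evenly over 12w0d to 19w6d (56 days, also an assumption), the shares are 13/56 = 23%, 6/56 = 11% and 0%.

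Reading all limits as ordinal weeks does not help. The last entry becomes 18w6d and the stop falls between 23w0d and 24w6d, which again leaves 29 to 42 days. Any time between admission and first dose for the Nugent result and second consent shortens this further if the 20-week limit is applied at admission; the article does not state its length.

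**Unequal standard.** With 12 planned weeks the threshold is 42/84 = 50% of the course. With six planned weeks it is 42/42 = 100%.

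**Early delivery or loss.** Six weeks are complete at 8w0d + 42 days = 14w0d for the earliest start and at 19w6d + 42 days = 25w6d for the latest. An event is therefore blocked from the adherent set only if it occurs within 42 days of starting, before about 26 weeks at the latest.

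Expected < 34 week events are 750 × 0.06 = 45 on placebo and 750 × 0.03 = 22.5 on intervention. If 5% to 20% of them fell within 42 days of starting (assumption), 2.25 to 9 placebo events and about 1.1 to 4.5 intervention events would leave an adherent set.

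**Possible bias.** Let both arms have a true risk of 6%, and let a share s of events be removed from numerator and denominator: r(s) = 0.06(1 − s) ÷ (1 − 0.06s).

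- Equal s in both arms: ratio 1, no distortion.
- s = 10% in one arm, 5% in the other: (0.054/0.994) ÷ (0.057/0.997) = 0.95.
- s = 20% and 10%: (0.048/0.988) ÷ (0.054/0.994) = 0.89.

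The removal shares are illustrative; the article gives no data on them.

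**The case against.** Several stronger readings are tempting, and the article does not support them.

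- **That late entrants can never reach six weeks.** The stop is only approximate, six weeks is given as the minimum duration, and a stop at 25w6d gives exactly 42 days. This stands: the lower end of the range is 0%. That reading leaves no slack, however, and the others leave a gap.
- **That early deliverers in general are excluded.** They are not. Deliveries from about 26 weeks up to 32 or 34 weeks are not blocked, nor are many earlier ones among women who started early.
- **That late entry biases the treatment comparison.** Gestational age at entry is fixed before randomisation and the limit is the same in both arms.
- **That entry at 8 weeks contradicts the 12-week maximum.** It does not. The stop is worded as an upper limit, so whichever of the two comes first satisfies both statements.
- **That the effective-treatment set is the adherent set.** This is never stated. It is a reasonable inference, since section 3.1 holds the only adherence definition, but a fuller protocol or analysis plan may build the set otherwise.
- **That the 7% to 15% explains the planned 15% adherence loss.** Section 3.4 (Sample size) does not say how that figure was derived.

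A flat minimum exposure is also a coherent idea of effective treatment. As an exposure threshold it can be defended. As a measure of adherence, with planned courses of different length and a requirement to remain undelivered, it cannot.

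**Conclusion.** The point holds in limited form. The stated rule does not fit the article's own entry limit and stop for the latest starters on most readings: about 15%, 7% or 0% are non-adherent by construction with a stop at 24w0d, 25w0d or 25w6d, assuming even entry over 8w0d to 19w6d. That part costs size and representativeness.

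The 42-day requirement is the part that can bias. It selects on the outcome after randomisation, but only for deliveries or losses within six weeks of starting. Under no true effect, unequal removal of the sizes assumed above would move the risk ratio to 0.95 or 0.89; equal removal would not move it. All of this depends on the effective-treatment analysis using the section 3.1 definition. Intention to treat is untouched, so this is a defect in one planned analysis and not in the trial's main comparison.

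**What to change.** Define adherence from the returned-capsule count that section 3.1 already provides for: capsules taken divided by capsules due, from first dose to the earlier of the woman's own planned stop or delivery/loss, with a cut-off fixed before unblinding. Early deliveries are then not removed by the outcome itself. State how the effective-treatment set is formed and present its result as supportive to intention to treat.

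Recruitment has finished, so only an analysis set changes. The costs are these:

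- The adherent set will differ from the one in the article.
- A woman who delivers after very short exposure can count as adherent.
- Capsules are counted at the post-treatment prenatal visit, so exposure in women who deliver before it may have to come from the questioning at earlier visits.

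The passages on entry limit, planned stop and six-week minimum duration must also be reconciled; no view is taken on which is right.
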